#### Observational data analysis plan

We will employ a rapid content analysis technique to extract the most salient information regarding the context and the recipients from these data [88]. The method is widely used in health services research, and has recently been used in implementation research to maintain rigor and produce a quick turnaround of results. As described earlier, we will follow a systematic process of examining and categorizing data. We will organize the emerging code under the domains of innovation, recipients, or context (informed by i-PARIHS) as they relate to implementation at each practice site and across practice sites.

### 3. Evaluating sustainability of facilitator-led implementation strategies

Since sustainability of public health interventions in FQHCs is a persistent challenge, we examine key contextual factors and explore their relationship with sustainability of strategies, using the Integrated Sustainability Framework (ISF) [89]. Sustainability is conceptualized as a dynamic and iterative process over time that is influenced by multiple determinants at the different socioecological levels [89, 90]. This framework lists factors relevant to clinical settings, categorized under the domains of *outer context* (i.e., sociopolitical context, leadership, funding, etc.), *inner context* (i.e., staffing, navigators, etc.), *intervention characteristics* (i.e., adaptability, fit, etc.), *implementation processes* (i.e., partnerships, trainings, etc.), and *implementer characteristics* (i.e., related to the provider). We will use the observational data collected during the implementation period to identify the factors that influenced implementation and use these as a base to further query about sustainability in FQHCs.

### Data collection

Twelve months after implementation, we will also conduct semi-structured interviews with implementation team to identify key factors that influence sustainability of the strategies over the next three-five years. We will use interviews to gain in-depth insight and explore the real-world complexity associated with sustaining interventions in FQHCs, as recommended in previous literature [89, 90]. Informed by the ISF [89] and the observational data collected during the implementation period, we will work with our study team to develop an interview guide consisting of open-ended questions. Similar data collection procedures will be followed as described in baseline assessment for implementation team interviews.

### Analyses

Data analyses will follow a systematic process of examining, categorizing and tabulating the data from the transcripts to answer the research questions [85]. The analysts will read the interview transcripts separately to look for concepts and ideas described by the participants. Based on the interview questions and the initial concepts, a codebook will be created consisting of codes and their definition. Data interpretation will be based on: actual words used by the respondents, frequency, extensiveness and intensity of concepts, and the larger trends that emerge from an accumulation of evidence [91]. We will create descriptive statements that summarize these codes under the specific domains as described in the ISF [89] and organize these in a matrix format. We will use quotes to highlight comparisons both within and between transcripts. To report the findings from the qualitative inquiry, a conceptually ordered display [92] will be created to showcase the relationships between the concepts to explain sustainability of the strategies and implementation outcomes in the FQHC context, across settings.

### Data management and confidentiality

The research team trained in human subjects research and ethics will protect participants' privacy and confidentiality by 1) removing personally identifiable information from study records, 2) assigning a unique numerical identifier to each participant for their records, and 3) conducting interviews in a closed office space to keep any private information learned during interviews confidential. The research coordinator will securely store paper records in a locked filing cabinet. The data manager will store electronic records on a password-protected database and back up on a secured server. The PI will retain study data that do not contain personally-identifying information indefinitely to allow for review and reanalysis of data. Record retention and destruction of identifiable data will take place in compliance with NIH policies governing record maintenance, retention, and applicable regulations.

### Data and safety monitoring plan

The Pl will monitor data and safety on a continual basis. Annual reports will be submitted to The University of Texas Health Science Center at Houston (UTHealth Houston), Institutional Review Board (IRB) and National Institutes of Health (NIH). An Independent Monitor for the proposed study will be designated to semi-annually review study accrual, adverse events, and preliminary findings (process and outcome) as they become available. We will use this information to make any necessary modifications to the study. All adverse events will be reported immediately upon hearing the UTHealth Houston, IRB and to our collaborating FQHC partners. This intervention is believed to have very few risks for participants, and we anticipate very few to no study-related adverse events. If adverse events are reported that appear study-related, severe, and in excess to that expected, they will be reported to National Institutes of Health.

### Ethics and dissemination

The UTHealth Houston, IRB, approved this study HSC-SPH-24-0335. The IRB approved this protocol, information sheets, training curriculum, and recruitment materials. If we need to make any modifications to the protocol which may impact on the conduct of the study, a formal amendment to the protocol will be submitted to UTHealth Houston IRB for approval and the PI will communicate changes to implementation collaborators.

### Consent process

Providers, staff, and parents will complete electronic* s*urveys remotely or in person. Research staff will obtain informed consent before pre-post surveys and document consent in REDCap. For remote interviews, research staff will obtain verbal consent from interviewees via video conference and document consent in REDCap. The participants for both surveys and interviews will receive a copy of the consent form via email. See Supplementary Files 4-7.

## Discussion

Despite HPV vaccine intervention research showing that focusing on implementation on multiple levels and using theory in intervention development are best practices, few interventions were multilevel and employed theory [52]. Additionally, implementation studies to increase vaccination in resource-limited settings like FQHCs [59–61], especially those serving low-income, uninsured/underinsured, and racial/ethnic minority populations, are limited. Our study addresses these gaps by focusing on multiple levels (provider and practice) and employing frameworks (i-PARIHS and ISF). The study will provide three main outcomes: a summary report of the baseline assessments, implementation and effectiveness outcome data, and observational data. First, the summary report includes vaccine coverage, provider performance, and practice characteristics the implementation team will utilize to select specific implementation strategies to increase vaccinations and will be included in their clinical practice plan. Second, the effectiveness and implementation outcome data will provide evidence for implementation efforts directed towards increasing vaccinations for Latino/a adolescents and in the long-term will reduce health disparities associated with HPV-associated cancers. Findings will also provide information on which implementation strategies work best in resource-limited practice settings to increase recommendations and vaccinations. Lastly, the observational data from the implementation period and the interviews will collectively contribute to the limited empirical literature around HPV vaccination-related implementation strategies and outcomes. These findings will help identify factors influencing sustainability, as perceived by implementation team that were involved in the implementation and help distinguish whether they are distinct from factors influencing implementation.

We also may encounter potential challenges related to quality assurance, retention, and training delivery involved in performing the study, but have devised alternative strategies to overcome these challenges. First, if practices are not able to generate vaccination status reports from their EHR, we have experience from our pilot in troubleshooting this problem and ensuring high assessment quality through extensive training and ongoing technical assistance for practice staff (remotely or by phone). The research team also has substantial experience in collecting data in person and remotely and in both English and Spanish. Another potential problem is clinical staff turnover, which we also have experience from our pilot troubleshooting by the external facilitator working closely with FQHC leadership to implement strategies and booster trainings for new staff. These trainings ensure the capacity of the practice for sustaining their clinical practice plans. Lastly, regarding training delivery, we are working with the TACHC to tailor the delivery (in person, remote or hybrid) of the training to fit FQHC needs. TACHC has extensive experience planning, delivering, and evaluating remotely delivered trainings with FQHCs. TACHC has agreed to provide infrastructure support, guidance, and coordination for transitioning provider and immunization navigator training to a remotely delivered model and implementing monthly problem-solving meetings across practices.

In conclusion, the findings of this study will advance our understanding of implementation research in resource-limited practices that serve populations experiencing substantial disparities, and to identify strategies that improve delivery and increase vaccine uptake. Findings from the current study will inform national implementation efforts and contribute towards future research targeting dissemination and scale-up, key foci for health equity focused implementation research.

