## Methods

### Overall design

The purpose of TRUE SYNERGI is to test the implementation and effectiveness of provider- and practice-level strategies aimed at increasing vaccination rates, first in a larger sample of practices and second, to improve our understanding of what combination of strategies influence provider recommendations and practice-level vaccination rates and under what conditions. We use a hybrid type 2 study design [66], focusing on understanding implementation aspects of an HPV vaccination focused set of strategies in a FQHC setting [66–68]. We are using a stepped-wedge, cluster randomized trial, among three predominantly Latino serving FQHCs with nine practice sites in Texas. We selected this design due to logistical, practical, and financial constraints in FQHC settings that make it more feasible for implementation to take place in stages [69] (See Table 1).

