### Conceptual framework

Figure 1 shows the conceptual framework for this study [70, 71].Given the feasibility shown by TRUE SYNERGI, the external facilitator will use a participatory approach to implement these strategies: provider education, assessment and feedback, technical assistance, training and education for the clinical staff, immunization navigator, and development of the clinical practice plan. We will examine the mechanisms by which these strategies influence the implementation outcomes at the level of the parent/patient, provider, and clinical practice using both qualitative and quantitative methods. Given this is an implementation trial, we will measure both effectiveness (i.e., HPV vaccination initiation and completion among 11–12 year olds and among 13–17 year olds) and implementation outcomes (i.e., number of providers giving HPV vaccine recommendations, number of vaccine doses provided, number of patient reminders/recalls made for vaccine completion, and confidence among parents in vaccinating their children).

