### RCT provider and practice-level implementation strategies

The facilitator-driven implementation strategies used to increase HPV vaccine uptake in rural FQHC practices [29, 65] include development and implementation of a clinical practice plan, provider education, assessment and feedback plus technical assistance, and immunization navigator training and education.

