### 2. Implementation of facilitator-led implementation strategies

Implementation strategies are methods or approaches that promote implementation indicators or outcome [86]. We will be focusing our efforts on the provider- and practice-level strategies described above. We will document the facilitation-driven implementation strategies selected by the clinical practice in their clinical practice plan. The i-PARIHS framework [63] will guide our understanding of the implementation of each of these strategies in the FQHCs. We will utilize the i-PARHS framework to guide the monthly meetings that will provide technical assistance if needed, assist in problem solving, and conduct a check-in, during the implementation period (defined as the first year after the start of project activities). Observational data in the form of monthly meeting notes and external facilitator debriefs will provide an in-depth understanding of the complex and dynamic *context* and the *recipients* (e.g., providers, immunization navigators, FQHC leadership) involved in the implementation at the practice settings. Baseline assessment findings will provide an in-depth understanding of the *context* and the *recipients*, which will enable the external facilitator to promote tailored implementation of strategies during implementation. We will utilize the i-PARIHS framework to review progress pre- and post-implementation and evaluate how strategies influenced implementation.

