#### Statistical analysis plan

The same analytic strategy will be applied to each age group (11–12 vs. 13–17) for each HPV outcome separately. Both patient level characteristics (e.g., gender and ethnicity) and practice level characteristics (e.g., practice location and size) will be summarized using descriptive statistics and compared across the three FQHC groups using ANOVA or Kruskal-Wallis test for continuous variables and Chi-square or Fisher’s exact test for categorical variables. To compare the effect of facilitator-driven implementation strategies during the exposure period with the control period on the binary HPV outcomes, generalized linear mixed models (GLMMs) will be used with fixed effects for time and intervention as well as a random effect for practice, while considering patient-level and practice-level characteristics as needed. Heterogeneity of intervention effects will be examined by testing the interaction terms between intervention and potential effect.

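### The stated conclusion about which strategies, or combinations of strategies, work best exceeds a design that contrasts only the whole facilitated package with control

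*Protocol article*

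**What the plan says.** **The promised conclusion.** The Discussion states: "Findings will also provide information on which implementation strategies work best in resource-limited practice settings to increase recommendations and vaccinations". That sentence directly follows the one on effectiveness and implementation outcome data; the observational data are introduced after it. Overall design gives as the second purpose of the trial "to improve our understanding of what combination of strategies influence provider recommendations and practice-level vaccination rates and under what conditions".

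**What is delivered.** Under Conceptual framework, "the external facilitator will use a participatory approach to implement these strategies: provider education, assessment and feedback, technical assistance, training and education" and further elements. The section on provider- and practice-level strategies says that they "include development and implementation of a clinical practice plan, provider education, assessment and feedback plus technical assistance, and immunization navigator training and education". Neither section withholds any of these from a practice. Practices also tailor: section 2 says "We will document the facilitation-driven implementation strategies selected by the clinical practice in their clinical practice plan", and section 1 (Baseline assessments) says that each practice's baseline data guide the choice.

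**What is randomised.** Setting and randomization, and Data collection in section 2, randomise the three FQHCs to start first, second or third. An FQHC's three practices share one cluster.

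**What is analysed.** The Statistical analysis plan section sets out the contrast: "To compare the effect of facilitator-driven implementation strategies during the exposure period with the control period on the binary HPV outcomes". For this, "generalized linear mixed models (GLMMs) will be used with fixed effects for time and intervention as well as a random effect for practice". It adds: "Heterogeneity of intervention effects will be examined by testing the interaction terms between intervention and potential effect". That sentence names no modifiers. Table 4 gives detectable differences between the control and intervention periods.

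**The concern.** To say that one strategy, or one combination, raises vaccination more than another, the trial needs outcomes contrasted between strategies. The stated design assigns no such contrast, and the stated model has no term that separates one strategy from another. Whatever differs between practices was chosen by the practices themselves in the light of their own starting position. Baseline performance, staffing and context would therefore travel with the strategy.

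At stake is what the trial may conclude. FQHCs reading the results could adopt or drop particular strategies on the strength of differences between a few self-selected practices, believing that a randomised trial stood behind the comparison. This is not a detail that an analysis plan could supply: no analysis can create a randomised contrast that the design did not assign.

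**Working it through.** **1. The plan's own figures, and the contrast they describe.** Inputs from Sample size justification: 9 practices, 15 quarterly periods of which 14 are counted, 30 patients aged 11-12 per practice-quarter, ICC 0.026 (initiation) or 0.003 (completion), two-sided alpha 0.05, 80% power.

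- Sample size: 30 × (15 − 1) × 9 = 3,780, as stated.
- Detectable difference = 2.8016 × SE, where 2.8016 is the sum of the normal quantiles for alpha and power. The SE comes from a linear mixed model with fixed period effects, **one** intervention term and a random practice effect, with variance at the control rate.
- The design matrix (Table 3) is not visible, so step timings were searched. One transition quarter with starts two quarters apart fits. Several placements of the first start fit equally well, so the timing is inferred, not read.

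| Outcome, control rate | Recomputed | Table 4 |
|---|---|---|
| Initiation, 0.2 | 0.0943 | 0.094 |
| Initiation, 0.5 | 0.1179 | 0.118 |
| Completion, 0.03 | 0.0392 | 0.039 |

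The figures reproduce, and they do so for a single package-on versus package-off term. No power figure in the protocol concerns a contrast between strategies.

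**2. Can the core strategies be separated?** Assume that the four core items in the strategies section all count as on from the same quarter in each practice. The four indicator columns are then identical. An intercept plus four indicators has 5 columns but rank 2, so only their joint effect can be estimated.

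**3. Can the practice-selected part be compared?** With k optional strategies there are 2^k possible combinations: 8 for k = 3, 16 for k = 4 and 32 for k = 5. There are 9 practices in 3 randomised units. The values of k are illustrative, since the protocol gives no number. Selection follows each practice's baseline data, so strategy and practice are confounded however many records are pulled.

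**4. How far can practices differ by chance alone?** This is illustration only. Give all nine practices the same true change and look at the gap between the largest and smallest observed control-to-intervention change.

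*(a) Sampling error only*, from 0.30 to 0.408 (Table 4's row for a 0.3 control rate), with a control quarters and b intervention quarters, a + b = 14:

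SE = √[0.30 × 0.70/(30a) + 0.408 × 0.592/(30b)]

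| a / b | SE of one practice's change | Mean gap, best to worst of 9 |
|---|---|---|
| 7 / 7 | 0.0464 | 0.138 |
| 4 / 10 | 0.0505 | 0.150 |
| 10 / 4 | 0.0521 | 0.155 |

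*(b) Simulation with assumed staggered rollouts*: 33% to 44% in every practice as a common log odds ratio, practice intercepts with ICC 0.026, no secular trend, 3,000 replicates each. Mean gaps are:

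- transitions at periods 2/4/6: 20.4 points;
- transitions at periods 4/6/8: 15.2 points;
- transitions at periods 6/8/10: 14.5 points.

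The largest figure reflects the first FQHC's practices having one control quarter, about 30 records each. Across (a) and (b) the gap is about 14 to 20 percentage points with no true difference in effect.

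**The case against.** **The wording is soft and the trial is mixed-methods.** The Discussion promises to provide information, and Overall design speaks of understanding and does not mention a best strategy. The three aims at the end of the Introduction include no comparison of strategies. Meeting notes, facilitator debriefs and interviews can show how strategies operated and under what conditions. All of that stands, and it is why descriptive and qualitative reporting belongs in the fix. Even so, saying which strategies work best to increase vaccinations is a comparative claim about outcomes, and qualitative data cannot supply that comparison on vaccination rates.

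**The model is more than one term.** This is correct: heterogeneity interactions are planned, and naming modifiers may be left to an analysis plan. If selected strategies were used as modifiers, however, the contrast would still be non-randomised, driven by baseline findings and confounded with practice.

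**Stronger readings that the protocol does not support.**

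- A reader might infer that practices or strategies will be ranked, so that a winner is always declared. No ranking rule or best-practice comparison is stated.
- A reader might set the 14 to 20 point gaps against Table 4's detectable differences. These are different quantities: one is the range of nine crude single-practice changes, the other a pooled, model-based contrast. The gaps cannot be read as an error rate of the trial.
- A reader might infer that the hope of informing national efforts rests on a strategy ranking. The abstract ties it to the findings as a whole.

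**Conclusion.** The point holds for the stated conclusion. Overall design and the Discussion announce strategy-level effectiveness findings; the randomisation, the model and the power calculation support one effectiveness conclusion, the effect of the facilitator-led package against control. Separate effects of universally delivered core strategies are not estimable (rank 2 of 5, assuming that they start together). Comparisons of practice-selected strategies would be observational, spread over nine practices in three randomised units.

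The 14 to 20 point gaps rest on assumed step timings, assumed rates and no secular trend. They show only that sizeable differences between practices are expected by chance, and the verdict does not depend on them. Nothing here questions the primary package comparison, its sample size or its data collection.

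**What to change.** In Overall design and in the Discussion:

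- State that the randomised comparison estimates the effect of the facilitator-led package.
- Replace the statements on which strategies work best and which combinations are influential with a descriptive and qualitative report of the strategies each practice selected and how they were carried out.
- Label any comparison of outcomes by strategy or combination as exploratory and non-randomised, give confidence intervals, and claim no best strategy. If selected strategies are to serve as modifiers in the heterogeneity tests, the same label applies.

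**Cost:** a change of wording, with no new data and no change to the primary analysis. The stated deliverable becomes less ambitious. Clearly labelled exploratory work remains possible.
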